### Analysis of primary outcome (AIM 1)

In the primary analysis, the rates of clinical *P. falciparum* malaria in children 6–24 months of age will be compared between treatment arms by estimating the incidence rate ratio and a corresponding 95% confidence interval (with the control arm as the referent group) of malaria using a Poisson regression model. The outcome, the number of observed incident cases of malaria, is a count variable. Individuals will be censored from the analysis for a period of 28 days after an incident malaria episode to account for the reduced risk of infection following treatment with AL. The Poisson model will include adjustments to control for stratification variables from randomization (study site and age group) and will include an offset to account for varying person-time-at-risk across subjects. The robust variance estimator will be used to account for potential overdispersion.

In exploratory analyses, we will further evaluate our primary outcome by fitting additional Poisson regression models to estimate associations between the incidence of malaria and measured covariates, including the frequency of *lesu* use and washing and residual permethrin concentration among participants in the intervention arm.

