# STUDY DESIGN

The proposed study is a double-blind, randomized controlled trial of permethrin-treated *lesus* to prevent *P. falciparum* malaria in children 6–18 months of age at study enrollment conducted at two sites in rural western Uganda. Participants will be randomized to one of two arms: permethrin-treated (intervention) or untreated (control) *lesus.* Participating mother-infant pairs will receive a new LLIN and two permethrin-treated or untreated *lesus* at enrollment. The total sample size will be 400 mother-infant pairs with 200 pairs in each arm. We will follow participants longitudinally for six months. Participants will be instructed and incentivized to present to one of the two study clinics when a fever develops, where they will be evaluated, tested, and treated, if positive, for malaria. Participants will also attend scheduled clinic visits every two weeks for routine surveillance of adverse effects and to test for asymptomatic infection. Re-treatment and sham re-treatment of *lesus* will occur each month.

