## Treatment Assignment Procedures

### Randomization Procedures

Participants will be randomized in a 1:1 ratio between intervention and control arms with randomization stratified by age group (age 6–11 months and 12–18 months) and by study site (Bugoye and Malaiba sub-counties). We will utilize stratified randomization to ensure an even distribution between arms at each clinical site and within each age group. Blocks will be variable in size to ensure allocation concealment. The randomization protocol will be developed and implemented by a University of North Carolina at Chapel Hill (UNC) biostatistician not involved in the direct enrollment of participants. Statistical software will be used to generate the list of random assignments with a 1:1 ratio. The randomization sequences will then be uploaded to the Research Electronic Data Capture (REDCap) database. Participants will be randomized upon enrollment using the REDCap Randomization Module on portable tablet devices equipped with cellular internet capability. Participants and health center staff but not research staff will be blinded to the allocation. Sham treatments and re-treatments of *lesus* will be employed to maintain blinding.

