## Household Survey

After enrollment is complete, study staff will:

- Record the household location using a handheld GPS device or smart phone.
- Document demographic and household characteristics via a questionnaire modified from the most recent Demographic and Health Survey [21].
- Perform a malaria RDT on both mother and child and if positive, receive weight-based treatment with AL, which is first-line therapy for uncomplicated malaria in Uganda [42].
- Issue a new LLIN (Permanet® 2.0, Vestergaard S.A., Switzerland) with guidance that it should be utilized to protect the child.
- At the conclusion of the survey, study staff will make an appointment date for the first clinic visit and provide the participant with an identification card, including the unique study ID number and telephone contacts.

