## Sample Size Considerations

The sample size was selected to provide sufficient power to evaluate the primary study hypothesis. We plan to recruit and enroll 400 mother-infant pairs. Additional participants will be enrolled in the study to replace those who drop out before 12 weeks. Those who drop out after 12 weeks will not be replaced. All participants who attend any clinic visits post randomization will be included in the primary, intention-to-treat (ITT) analysis.

Assuming a baseline risk of approximately 3.0 cases per 100 person-weeks as estimated from our pilot study, the trial will have power of at least 0.80 to detect a 30% relative reduction in the incidence rate of malaria between intervention and control groups over the proposed study period of 24 weeks with a type I error rate of 0.05 and assuming a two-sided test based on the asymptotic test statistic of the intervention parameter from a Poisson regression model with an offset for time at risk [49]. Power for other effect sizes is presented in the table below. This assumes an average of 23.1 weeks of follow-up per participant per arm, based on the observed drop-out in the pilot study. Calculations were conducted using nQuery software and are based on previously described methods [50].

No interim analyses are proposed, so no adjustments were made to these calculations to account for interim testing. This effect size was assessed as the minimum at which the intervention would be persuasive to take to scale, especially as it represents an incremental effect above and beyond LLIN use.

Anticipated Power to Detect Differences in Malaria Incidence Rate between Intervention and Control Arms

| **Rate Ratio** | **Anticipated Power** |
| --- | --- |
| 0.80 | 0.42 |
| 0.75 | 0.62 |
| 0.70 | 0.80 |
| 0.65 | 0.92 |

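### The primary Poisson model is valid, but pre-specifying each child's household-visit RDT result as a covariate would recover a modest, assumption-dependent amount of precision

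*Protocol*

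**What the plan says.** Protocol section 10.3.1 compares malaria rates with a Poisson regression that has an offset for time at risk and a robust variance. On covariates it states: "The Poisson model will include adjustments to control for stratification variables from randomization (study site and age group". The further covariates in that section (lesu use, washing, residual permethrin) belong to exploratory models and are all measured after allocation.

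Section 6.2 (Household Survey) has staff "Perform a malaria RDT on both mother and child", and positives are treated with AL. Section 6.1.2 dates the household visit to Day -21 to -7, and Appendix A2 lists the test for every child. Lesus are issued at the baseline clinic visit on Day 0 (section 6.3), where a dried blood spot for later qPCR is also taken. The intervention therefore cannot affect the household RDT.

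The order of RDT and randomization is not fixed. Section 6.2 lists the RDT among steps that follow enrollment, section 4.4.1 randomizes at enrollment, and Appendix A1 puts randomization at the same home visit.

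**The concern.** A child's malaria status before the intervention is a plausible individual marker of exposure. Two site strata and two age strata cannot capture differences between villages or between children. Whatever they miss stays in the residual as overdispersion. The robust variance then widens the interval to reflect it, which is honest but recovers no precision.

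The design has little room for that loss. Section 10.2 bases its power claim on a Poisson calculation and mentions no allowance for overdispersion, while section 10.3.1 expects that overdispersion may occur. With a log link and a treatment effect that is constant across baseline status, adding the covariate leaves the target rate ratio unchanged. What is at stake is precision and protection against chance imbalance, not validity.

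**Working it through.** **Inputs from the Protocol.** Section 3: "The total sample size will be 400 mother-infant pairs with 200 pairs in each arm". Section 4.4.1: "Participants will be randomized in a 1:1 ratio between intervention and control arms". Section 10.2: "Assuming a baseline risk of approximately 3.0 cases per 100 person-weeks as estimated from our pilot study"; "power of at least 0.80 to detect a 30% relative reduction in the incidence rate of malaria"; "type I error rate of 0.05 and assuming a two-sided test"; "This assumes an average of 23.1 weeks of follow-up per participant per arm".

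**Assumptions, not in the Protocol.**
- A share p = 7% to 30% of children is positive at baseline. This range is suggested by the 7.3%, 17.4% and roughly 30% parasite rates under Study Site & Population.
- The later malaria rate in positive versus negative children has ratio R = 1.5, 2 or 3.
- Other between-child overdispersion k (gamma variance) is 0 or 1.0.

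**1. The plan's own figure.** Expected events are 200 × 23.1 × 0.03 = 138.6 (control) and 0.70 × 138.6 = 97.0 (intervention).
- Unpooled variance of the log rate ratio: 1/138.6 + 1/97.0 = 0.01752, SE 0.1324. With |ln 0.70| = 0.3567, power = Φ(0.3567/0.1324 − 1.96) = 0.769.
- Pooled null variance: Φ(0.3567 × √(235.6/4) − 1.96) = 0.782.
- With the full 24 weeks, two-sided variants give 0.784 to 0.797.

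The stated 0.80 is thus reproduced within two points by the pooled form or by 24 weeks.

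**2. Variance with and without the covariate.** Leaving a binary marker out adds a relative variance between children of

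CV² = p(1−p)(R−1)² / (1 + p(R−1))².

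- Unadjusted: V = 0.01752 + (2/200) × [(1+k)(1+CV²) − 1].
- Adjusted: V = 0.01752 + (2/200) × k(1+CV²).
- The difference is 2CV²/200 for any k.

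Example with R = 2, p = 0.30, k = 0: CV² = 0.21/1.69 = 0.1243. The unadjusted V is 0.01752 + 0.00124 = 0.01876, and the cut is 0.00124/0.01876 = 6.6%.

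Each cell gives p = 7%, then p = 30%. Power is unpooled Wald at a rate ratio of 0.70.

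| R | CV² | Cut, k = 0 | Power without → with, k = 0 | Cut, k = 1.0 | Power without → with, k = 1.0 |
|---|---|---|---|---|---|
| 1.5 | 0.015; 0.040 | 0.9%; 2.2% | 0.765 → 0.769; 0.759 → 0.769 | 0.5%; 1.4% | 0.571 → 0.573; 0.563 → 0.569 |
| 2 | 0.057; 0.124 | 3.1%; 6.6% | 0.755 → 0.769; 0.740 → 0.769 | 2.0%; 4.1% | 0.558 → 0.567; 0.539 → 0.557 |
| 3 | 0.200; 0.328 | 10.3%; 15.8% | 0.723 → 0.769; 0.696 → 0.769 | 6.4%; 9.6% | 0.519 → 0.546; 0.489 → 0.529 |

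At R = 1 there is no gain (0.769 either way). The adjusted power never exceeds 0.769, the homogeneous-Poisson value by the same formula.

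**3. Effect of AL given to RDT-positive children.** Section 10.3.1 works with a 28-day period of reduced risk after AL. Counted from Day -21 to -7, it ends between Day 7 and Day 21, so it covers 7/168 = 4% to 21/168 = 12.5% of follow-up. If risk were zero in that time, R = 2 would fall at most to 2 × (1 − 0.125) = 1.75. CV² is then 0.0651 × 0.5625/1.0525² = 0.033 at p = 7% and 0.21 × 0.5625/1.225² = 0.079 at p = 30%. With k = 0 the cut is 1.9% to 4.3% instead of 3.1% to 6.6%.

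**The case against.** The strongest reply is that nothing here is wrong. A Poisson model with an offset, the stratification factors and a robust variance is valid and matches the randomization. Section 10.3.1 says what the model will include, not that it excludes everything else, and the separate SAP, which is not shown, may name more covariates. This stands, and it is why the point is a suggestion and not an error.

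Three further objections stand in part.
- **Heterogeneity.** The parasite rates under Study Site & Population come from different survey years, areas and ages. The figure of about 30% is for children aged 2 to 8 years, and the trial intends to recruit from high-transmission villages. A reader might infer a measured spread of exposure among trial children, but these figures do not provide one.
- **Size of the gain.** It rests on an assumed R, and it shrinks if baseline infection overlaps with site or age group, which are already in the model. AL treatment of positives may also weaken the association early in follow-up.
- **Cost.** A reader might call the covariate free. It needs no new data, but under the complete-case plan in section 10.3 a missing result could drop a child. The RDT might also be read after allocation by research staff, whom section 4.4.1 leaves unblinded.

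None of these shows a material loss from adding a well-defined covariate.

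**Conclusion.** The point holds as a low-priority efficiency improvement. With 7% to 30% positive and no other overdispersion, the variance of the log rate ratio falls by about 1-2% at R = 1.5, 3-7% at R = 2 and 10-16% at R = 3. With residual overdispersion of 1.0 the cuts are about 0.5-1.4%, 2-4% and 6-10%.

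In sample-size terms with k = 0, 400 × (V unadjusted / V adjusted − 1) is about 13 to 28 pairs at R = 2 and 46 to 75 at R = 3. All of this depends on an R that the Protocol does not give, and it takes no account of overlap with site and age group.

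Two stronger readings are not supported. One is that the planned model is biased or mis-specified; it is not. The other is that adjustment would secure or raise the stated power of 0.80. It can only return what between-child differences take away, up to about 0.77-0.78 at 23.1 weeks.

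**What to change.** Before unblinding, amend section 10.3.1 (or state in the SAP) as follows:
- Add the child's household-visit RDT result, under one definition, as a covariate beside site and age group. Do not leave a choice between RDT and Day 0 qPCR.
- State that the result is recorded before allocation is revealed, and make sections 4.4.1 and 6.2 and Appendix A1 agree on that order.
- Keep children with a missing result in the model, for example through a missing-result category, so that the complete-case rule does not remove them.
- Report the model with site and age group only as a sensitivity analysis.

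The cost is one extra parameter (two with a missing-result category) and a few sentences, with no new data collection. The downside is a small, possibly negligible gain if baseline status turns out to be weakly prognostic.

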### Analysis of secondary outcomes (AIM 2)

- Change in child’s Hb level from baseline to weeks 12 and 24, Change in child’s growth from baseline to weeks 12 and 24, Change in mother’s Hb level from baseline to weeks 12 and 24: For each endpoint, Student’s t tests will be used to compare mean changes between study groups at 12 and 24 weeks, with corresponding 95% CIs. Wilcoxon rank sum tests will be conducted as a sensitivity analysis. Participants with missing data at a given timepoint will be excluded from the analysis if missing data is minimal (<10% in both arms). If missing data are more common than anticipated, multiple imputation will be conducted.
- Asymptomatic parasitemia in children, Clinical malaria in mothers: Each endpoint will be analyzed using the same methods as the primary analysis of the primary endpoint. As in the primary analysis, ITT analyses with complete data are expected, but sensitivity analyses will be conducted if dropout or missing data are more common than anticipated or if adherence is lower than expected.
- Hospitalization for malaria: the number of hospitalizations for malaria in the treatment and control arms will be compared using Fisher’s exact test. Confidence intervals for the proportion of hospitalizations and the difference in proportions between randomization arms will be computed using Clopper-Pearson exact binomial confidence intervals.
- Safety measures (adverse reaction to treated-*lesu,* SAE): Descriptive analyses will be used to summarize adverse reactions to treated-*lesu* and SAEs, by treatment arm. A 95% 1-sided Clopper-Pearson exact binomial upper confidence limit for the probability of an SAE will be computed within each arm, and if sample sizes allow, by child’s age group.

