## Study Outcome Measures

| **Study Measure** | **Method of Collection** |
| --- | --- |
| 1. Primary Outcome |  |
| 1.A. Incidence of clinical malaria in child | (1) Acute febrile illness AND positive RDT at scheduled or unscheduled study clinic visit  - or -  (2) Written documentation of fever AND positive RDT from non-study clinic visit |
| 2. Secondary Outcomes |  |
| 2.A. Change in child’s Hb level | Hb measured at baseline (Week 0), Week 12, and Week 24 visits using HemoCue® device. |
| 2.B. Change in child’s growth measures | Height, weight, measured at baseline (Week 0), Week 12, and Week 24 visits. |
| 2.C. Change in child’s nutritional status | MUAC measured at baseline (Week 0), Week 12, and Week 24 visits [22]. |
| 2.D. Asymptomatic parasitemia in children | Presence of malaria parasites on bi-weekly dried DBS as determined by qPCR. |
| 2.E. Hospitalization for malaria | Self-reported history of hospitalization on bi-weekly questionnaire AND confirmation by study staff. |
| 2.F. Clinical malaria in mother | Same as 1.A. |
| 2.G. Change in mother’s Hb level | Same as 2.A. |
| 2.H. Burden of care-seeking | Self-reported history of clinic visits, work days missed, health expenditures on bi-weekly questionnaires. |
| 3. Safety Measures |  |
| 3.A. Adverse reaction to treated-*lesu* | Self-reported history on bi-weekly questionnaire and confirmation by clinical staff. |
| 3.B. Severe adverse event (SAE) | Care-seeking, hospitalization, or death attributable to the intervention. |
| 4. Covariates of Interest |  |
| 4.A. Socioeconomic status | Questions from baseline survey on ownership of mobile phone, vehicle, etc. [34] |
| 4.B. Maternal education | Self-reported history on baseline questionnaire. |
| 4.C. Frequency of *lesu* use and washing | Self-reported history on bi-weekly questionnaire, use diaries, direct observation. |
| 4.D. Residual permethrin levels | Punches of *lesu* cloth taken at 2-, 4-, 6-month visits tested by gas chromatography [35] |
| 4.E. *Anopheles* mosquito density | CDC light trap collections in peri-domestic space (indoor/outdoor) with species identification |

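### Unadjusted t tests on change in Hb and growth leave out the randomisation strata and use baseline inefficiently (valid, but wider intervals than needed); separately, Clopper-Pearson cannot give an interval for a difference between arms

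*Protocol*

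**What the plan says.** Protocol section 10.3.2 (Analysis of secondary outcomes) fixes the method for change in child Hb, child growth and mother's Hb: Student's "t tests will be used to compare mean changes between study groups at 12 and 24 weeks". The stated alternative is also unadjusted: "Wilcoxon rank sum tests will be conducted as a sensitivity analysis".

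Section 4.4.1 (Randomization Procedures) describes "randomization stratified by age group (age 6–11 months and 12–18 months) and by study site", and gives the purpose: "We will utilize stratified randomization to ensure an even distribution between arms at each clinical site and within each age group". Section 10.3.1 carries those factors into the primary analysis: "The Poisson model will include adjustments to control for stratification variables from randomization (study site and age group"). Section 10.3.2 applies the primary method to asymptomatic parasitemia in children and clinical malaria in mothers, but not to the continuous outcomes.

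The baseline values exist. For child Hb, the table in section 2.2 has "Hb measured at baseline (Week 0), Week 12, and Week 24 visits using HemoCue® device"; child height and weight follow the same timetable, and mother's Hb refers back to child Hb.

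For hospitalization, section 10.3.2 tests between arms with Fisher's exact test, and says that the interval for "the difference in proportions between randomization arms will be computed using Clopper-Pearson exact binomial confidence intervals".

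**The concern.** There are two separate matters.

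The first is efficiency. With randomisation balanced within strata, part of the variation between children is removed from the arm comparison by design. A two-sample t test still counts that variation in its standard error, so the interval is too wide wherever the strata predict the change. In addition, subtracting the baseline amounts to adjusting for it with the slope fixed at 1, which is generally not the slope that minimises the variance. These outcomes are under false discovery rate control (section 10.3), so precision lost here makes a real effect harder to declare.

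The second is a misnamed method. Clopper-Pearson inverts the binomial test for one proportion. It defines no interval for p1 − p2, so the step cannot be carried out as written and the analyst would have to choose a substitute.

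**Working it through.** The protocol states no power, SD, correlation or sample size for the secondary outcomes, so there is no figure to reproduce. Inputs from the protocol: 200 pairs per arm (section 3), 1:1 allocation in 2 × 2 = 4 strata (section 4.4.1), two-sided α = 0.05 (section 10.3). Assumed, because not given: the correlation rho between baseline and follow-up, the SDs s0 and s1 at baseline and follow-up, and the share R² of the variance of change explained by the strata.

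**Strata.** After balanced stratified randomisation, the true variance of the mean difference is (1 − R²) times the variance that the unadjusted t test estimates. Its actual type I error is therefore 2(1 − Φ(1.96/√(1 − R²))). Where the stratum-adjusted analysis has 80% power, the unadjusted one has Φ(1.96 + 0.842 − 1.96/√(1 − R²)).

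| Assumed R² | Type I error, formula | Simulated, unadjusted | Simulated, stratum-adjusted | Power of the t test when the adjusted analysis has 80% |
|---|---|---|---|---|
| 0.05 | 0.044 | 0.043 | 0.048 | 78.5% |
| 0.10 | 0.039 | 0.039 | 0.050 | 76.9% |
| 0.20 | 0.028 | 0.028 | 0.049 | 72.9% |

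The simulations used 60,000 trials of 400 participants in 4 equal strata for each R².

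**Baseline.** Per participant:

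- Var(change) = s0² + s1² − 2·rho·s0·s1
- Var(adjusted) = s1²(1 − rho²)
- Difference = s0² − 2·rho·s0·s1 + rho²·s1² = (s0 − rho·s1)²

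The difference is never negative, so in large samples adjustment cannot do worse than the change score. It is zero when s1/s0 = 1/rho.

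If s0 = s1, then Var(change) = 2s²(1 − rho), Var(adjusted) = s²(1 − rho²), and the ratio is (1 + rho)/2:

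| Assumed rho | Variance ratio | Number per arm, adjusted, matching 200 on change | Power, adjusted, when the t test has 80% |
|---|---|---|---|
| 0.3 | 0.65 | 130 | 93.5% |
| 0.5 | 0.75 | 150 | 89.9% |
| 0.7 | 0.85 | 170 | 86.0% |
| 0.9 | 0.95 | 190 | 82.0% |

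The table depends on equal variances. At rho = 0.9 the gain vanishes if s1/s0 = 1/0.9 = 1.11, that is, if the follow-up SD is 11% larger.

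**Interval for the difference.** Take assumed counts of 5/200 and 15/200. The Clopper-Pearson limits are 0.8% to 5.7% and 4.3% to 12.1%. One possible improvisation is to subtract opposite limits: 0.82 − 12.07 = −11.3 and 5.74 − 4.26 = +1.5 percentage points. Newcombe's two-sample interval is −9.7 to −0.7. Fisher's exact test gives p = 0.036 on the same counts, so here the improvised interval includes zero while the planned test rejects.

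**The case against.** The strongest reply is that the first part concerns a preference, not an error. The outcomes are defined as changes, a t test on change is unbiased, and where the strata matter its type I error lies below 0.05. The outcomes are secondary and the primary conclusion is untouched. All of that stands.

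Four stronger readings are tempting, and the protocol does not support them:

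- **That the Hb and growth comparisons are biased.** Chance baseline imbalance can move a single estimate through regression to the mean, but over randomisation this averages out and the t test's standard error already reflects it.
- **That a change score is always less precise when rho is below 1.** The algebra shows equality at s1/s0 = 1/rho; the (1 + rho)/2 ratio needs equal variances at the two visits.
- **That the gain for growth can be quantified.** No correlation, SD or age effect is given. The analysis text does not say whether growth is analysed raw or standardised for age, and standardising could remove much of any effect of the age stratum.
- **That a repeated-measures model over both visits is an equal substitute.** It treats missing visits differently from the complete-case and multiple-imputation rules in section 10.3.2 and would have to be reconciled with them.

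For mother's Hb, the age stratum is the child's age, and no gain in precision from it is claimed. The hospitalization point is narrow: Fisher's test and the interval for each arm's proportion are sound, and only the interval for the difference is affected. The 5 versus 15 counts are illustrative, and in that example the improvised interval errs towards caution.

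What remains is that the protocol itself fixes these methods, departs without a stated reason from its own practice for the primary outcome, and names a one-sample method for a two-sample quantity.

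**Conclusion.** The point holds in two parts of different kinds.

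The t tests are valid but less efficient than the collected data allow. The direction is secure: adjustment for baseline is never worse in large samples, and leaving out predictive strata makes the interval too wide. The size is not established. It rests on assumed R² of 0.05 to 0.20 (true type I error 0.044 to 0.028) and assumed rho of 0.3 to 0.9 with equal variances (variance ratio 0.65 to 0.95). This is a worthwhile improvement to secondary analyses, not a threat to the trial's conclusion.

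Naming Clopper-Pearson for the difference in hospitalization proportions is wrong as written. That conclusion needs no assumption.

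**What to change.** In section 10.3.2:

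1. For child Hb, each growth measure and mother's Hb, replace the t tests by a linear model at week 12 and another at week 24, with the value at that visit as outcome and arm, baseline value, site and child's age group as covariates. Report the adjusted mean difference with its 95% CI. With baseline in the model, the arm coefficient is the same whether the outcome is the value or the change, so the results can still be presented as differences in change.
2. Keep the stated missing-data rules and the Wilcoxon test as sensitivity analysis.
3. For hospitalization, keep Fisher's test, keep Clopper-Pearson for each arm's proportion of participants hospitalized, and name a two-sample interval (for example Newcombe or Miettinen-Nurminen) for the difference.

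The cost is a change of wording before unblinding. All the variables are already collected, and no visit, sample or participant is added.
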